#### Primary outcomes

The primary outcome variables from the motion analysis, MTC magnitude, and variability, will be assessed using biomechanical assessment data at baseline and after training, which occurs immediately following the final training session after a minimum of 20 min rest. Retention MTC data at one, three, and six months for the affected limb will determine whether the target MTC, i.e. baseline MTC plus 1 SD, has been maintained after visual biofeedback training has concluded. The precise probability of tripping due to foot-ground contact will be computed by statistically modelling the MTC histogram [7].

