The aim of this project is to determine whether real-time biofeedback of toe clearance during gait training can significantly minimize tripping risk in people with stroke. We will test the efficacy of real-time biofeedback as an intervention to increase MTC using a randomized controlled trial (RCT) design incorporating both a training or “acquisition” phase with biofeedback. Retention tests will be conducted to confirm *learning*, as demonstrated by the longer-term or “relative permanence” of the targeted behavior.

The primary objective is to determine whether real-time biofeedback of MTC during gait training will significantly increase MTC in people with stroke. We will also determine whether changes in MTC achieved on a treadmill transfer to overground walking. It is hypothesized that, compared to no-biofeedback training, visual biofeedback of foot clearance parameters during gait training will significantly increase toe-ground clearance (MTC) and MTC during biofeedback training will be retained in the longer term. It is also hypothesized that increases in MTC demonstrated in treadmill training will transfer to overground walking, such that tripping-risk in people with stroke is significantly reduced.

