### Intervention

All participants, both controls and those in the feedback intervention group, will walk on the treadmill following an identical schedule of training sessions. Self-selected walking speed will be determined following treadmill familiarization with a physiotherapist during the first clinical assessment visit. This self-selected walking speed will be recorded and each treadmill walking session will be conducted at the same walking speed. All participants wear a safety harness when treadmill walking and continue for up to 10 min with rest breaks as required. Previous research by the authors had determined 10 min to be comfortable maximum for this population. Participants will wear the same comfortable shoes for all walking activities.

Participants randomized to the intervention group undertake biofeedback gait-training using a real-time display of the affected limb’s swing phase trajectory, with toe clearance and the associated MTC event clearly shown. Motion analysis markers will be attached to the shoe and other body segments to calculate toe clearance parameters in real-time as per the established protocol [6]. *Target* MTC will be calculated as baseline MTC plus 1 SD. The feedback group will be asked to move their affected limb such that MTC falls between target MTC mean + 0.5SD and target MTC-0.5SD, projected as parallel lines on a screen in front of the treadmill [16, 17]. If baseline MTC cannot be calculated, target boundaries will be set using the *maximum* toe clearance (TC) with instructions to control foot motion within that target band. Borg Ratings of Perceived Exertion will be recorded after each session.

Biofeedback is presented for the first six sessions then progressively reduced (faded) across the remaining four sessions. During fading, one-third of the initial feedback will be available at the beginning of session 7, one-third in the middle for session 8, one-third at the end of session 9, and, finally, one-10th at the beginning and one-10th at the end of session 10. As indicated above, the control group will walk under the same conditions without either feedback or any instructions concerning their gait control. Adherence to the gait training program will be reflected in the number of training sessions successfully completed and the research team will monitor any non-adherence.

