### Data management and statistical analysis

All data will be stored via REDCap, an application specifically designed for the safe storage of clinical research data, for seven years. Only research personnel associated with the study will have access to the data and it will not be available to external agencies. Optotrak, IMU, and Pedar data will be coded so no personal information will be identified in the data. De-identified data will also be stored on a secure drive at the University. The patient’s gait kinematics are monitored as the project progresses to confirm no adverse effects of gait training, such as increased tripping risk. External auditing is not required in this study because all experimenters are trained to identify and record adverse events.

MTC data obtained from the treadmill walking will be analyzed using two intervention group comparisons and repeated measures ANOVA of the intervention groups and change scores, with post-hoc comparisons where relevant. Walking speed will be used as a co-variate due to its influence on MTC data. The between-subject factor will be treatment group (No-feedback and Feedback) with Time (pre-training baseline, post-training, one month, three months, and six months) being the within-subject factor.Between-group comparisons of MTC post-training will reveal effectiveness of the biofeedback gait training method in improving MTC.The within-subject analysis of the Feedback group will reveal the biofeedback effects on MTC by comparing each participant’s after intervention (post-training) data to that obtained in retention conditions, i.e. MTC data at one month (short-term retention) and at three months and six months (long-term retention).MTC data collected during overground walking during retention conditions will determine whether any changes in MTC are translated to overground walking.

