## Discussion

This innovative study will evaluate the impact of augmented sensory information for improving gait function, specifically foot-ground clearance, via visually presented biofeedback. The research findings will contribute to the broader falls prevention initiative by demonstrating the effectiveness of toe clearance biofeedback in making walking safer. It will also confirm whether faded feedback enhances learning by demonstrating how performance is affected immediately following training and whether it can be retained in the long term. If shown to be effective, there will be opportunities for biofeedback-training applications to other gait-impaired clinical populations. The project’s findings will contribute to understanding how stroke-related changes to sensory and motor processes influence the tripping risks of everyday walking. The protocol is, however, limited to people with chronic stroke capable of walking on a treadmill due to the continuous real-time feedback used for gait training.

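### Retention of the biofeedback benefit is assigned to a Feedback-only comparison, which cannot separate it from change shared with controls

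*Protocol article*

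**What the plan says.** The Protocol article deals with retention in several places.

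- **Background.** The gain hypothesis is comparative: "compared to no-biofeedback training, visual biofeedback of foot clearance parameters during gait training will significantly increase toe-ground clearance (MTC". The same sentence adds that "MTC during biofeedback training will be retained in the longer term".
- **Primary outcomes.** Follow-up MTC of the affected limb is to show "whether the target MTC, i.e. baseline MTC plus 1 SD, has been maintained after visual biofeedback training has concluded".
- **Data management and statistical analysis, model.** A repeated-measures ANOVA has treatment group as the between-subject factor, "with Time (pre-training baseline, post-training, one month, three months, and six months) being the within-subject factor". Change scores and post-hoc comparisons are also planned.
- **Same section, purpose of each comparison.** For the randomized groups: "Between-group comparisons of MTC post-training will reveal effectiveness of the biofeedback gait training method in improving MTC". Retention goes to an analysis inside the Feedback group, which compares each participant's "after intervention (post-training) data to that obtained in retention conditions, i.e. MTC data at one month (short-term retention"; the three- and six-month visits carry the long-term label. The text says that this within-group analysis will show how biofeedback affects MTC.
- **Intervention.** Both arms have the same session schedule, and "the control group will walk under the same conditions without either feedback or any instructions concerning their gait control".
- **Discussion.** The trial is expected to confirm whether faded feedback helps learning by "demonstrating how performance is affected immediately following training and whether it can be retained in the long term".

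**The concern.** Change from post-training to follow-up in one arm mixes two things: change in what biofeedback added, and change that would have happened anyway. The end of treadmill training, repeated testing and elapsed time apply to both arms. The Feedback group's own change contains all of them, yet the plan reads it as an effect of biofeedback.

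This can mislead in both directions. If both arms fall back equally once training stops, the named analysis shows a decline although the benefit over control is intact. If controls improve after training while the Feedback group stays level, it shows no decline although the benefit has shrunk. Retention is a stated hypothesis and a promised conclusion, so a reader will look for this result.

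**Working it through.** **1. The plan's own figure.** Sample size calculations gives f = 0.25, two time points, correlation 0.7, alpha 0.05, power 0.85 and N = 126. With the noncentral F for the between-group factor, lambda = f² × N × m / (1 + (m − 1) × rho) = 0.0625 × 126 × 2 / 1.7 = 9.26, on 1 and 124 degrees of freedom. Power is 0.855; N = 124 gives 0.8498. So 126 (63 per arm) reproduces. It covers baseline and post-training only, not the retention visits.

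**2. What the named contrast estimates.** Let F and C be the mean changes from post-training to a retention visit in the Feedback and control arms. The change in the between-group benefit is B = F − C, so F = B + C. The named analysis estimates F. It equals B only if C = 0, and otherwise it is off by exactly C. This is algebra and needs no assumed value.

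**3. Illustration in centimetres.** The pilot figures are mean MTC 1.4 cm and SD 0.77 cm, so baseline plus 1 SD is 2.17 cm. Suppose the Feedback arm is at 2.17 cm at post-training and at follow-up. Its change from post-training is 0, and it meets the target. Assumed control gains from baseline to follow-up:

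| Control gain (cm) | Benefit over control at follow-up (cm) |
|---|---|
| 0 | 0.77 |
| 0.2 | 0.57 |
| 0.4 | 0.37 |
| 0.77 | 0 |

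Both retention readings are the same in every row. A control gain already present at post-training would appear in the named post-training comparison. One that arises later would appear only in the group-by-time model.

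**4. Precision of the two contrasts.** Assumptions: 63 per arm, SD units with 1 SD = 0.77 cm taken as the between-participant SD, and correlation r = 0.7 between the visits compared. The protocol states 0.7 only for its two-time-point calculation, so r = 0.5 to 0.9 is shown as a range. The SD of a change is sqrt(2(1 − r)) = sqrt(0.6) = 0.775.

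- Within-arm 95% half-width: t(62) × 0.775 / sqrt(63) = 0.195 SD = 0.15 cm (r = 0.5: 0.252 SD; r = 0.9: 0.113 SD).
- Between-group 95% half-width on change from baseline: t(124) × 0.775 × sqrt(2/63) = 0.273 SD = 0.21 cm.
- Baseline-adjusted, with residual SD sqrt(1 − 0.49) = 0.714: 0.252 SD = 0.19 cm.

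**5. Can the planned size carry the between-group contrast?** On change from baseline, the difference detectable with 85% power is 0.417 SD = 0.32 cm (r = 0.5: 0.538 SD = 0.41 cm; r = 0.9: 0.241 SD = 0.19 cm). With alpha divided by three for three visits it is 0.479 SD = 0.37 cm. All are below the 0.77 cm target gain.

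**6. Sensitivity to an assumed shared change.** For a true shared decline of 0.1, 0.2 or 0.3 SD (0.08, 0.15, 0.23 cm) with the benefit over control fully kept, the within-arm test is significant with probability 17%, 52% or 86% at r = 0.7. The ranges over r = 0.5 to 0.9 are 12–42%, 35–94% and 65% to over 99%. These are powers to detect a real within-person change. They become misleading only when that change is read as loss of biofeedback benefit.

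**The case against.** The strongest reply is that the randomized evidence is already planned. The ANOVA has both arms and all five visits, with change scores and post-hoc comparisons, so group differences at one, three and six months come out of it. That stands. A reader might infer that the plan has no randomized evidence on retention; the documents do not support that.

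Second, retention can be a property of the learner. Background presents the retention tests as confirming learning, and the comparison with no-biofeedback training attaches most directly to the gain clause. Post-training against follow-up in those trained is a fair answer to that question. This also stands, and it is a reason to keep the analysis. It does not justify reading the result as an effect of biofeedback.

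Third, a reader might infer that baseline plus 1 SD and the post-training value are contradictory standards. They can disagree. With assumed values, 1.70 cm held at 1.70 cm shows no decline but is 0.47 cm below 2.17 cm; 2.60 cm falling to 2.20 cm is a 0.40 cm decline but 0.03 cm above it. But whether the target is still met and whether performance has decayed are two questions, and different answers to them are not a contradiction.

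Fourth, the choice of contrast might be left to a fuller protocol or SAP. Silence would be no finding. Here the article does assign the contrasts: between-group to post-training, Feedback-only to retention, with a causal reading of the latter.

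Finally, no document supports a shared change of any particular size. Participants are at least six months after stroke and have no walking or lower-limb physiotherapy while enrolled, which limits some sources of drift. So the percentages in step 6 are not demonstrated error rates.

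**Conclusion.** The concern holds in a limited form. The plan assigns retention to a one-arm comparison and gives it a causal reading that it cannot bear, while the randomized contrast sits unassigned in a model already planned. The bias equals the shared change, one for one; its size cannot be determined from the documents. The precision figures rest on 63 per arm and an assumed correlation of 0.7 between these visits. The primary post-training comparison, the training target and the sample size are untouched. The wording should be changed, because following it as written can give a wrong conclusion on a stated hypothesis.

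**What to change.** In Data management and statistical analysis, name the between-group MTC difference at one, three and six months as the evidence that the biofeedback benefit is retained. Take it from the planned group-by-time model, either baseline-adjusted or as change from baseline, with confidence intervals.

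Keep two descriptive results, each labelled with its own question: the Feedback group's change from post-training, with its interval (did performance decay?), and attainment of baseline plus 1 SD, reported in both arms (is the target still met?). State that a non-significant decline will not be read as retention. Drop the statement that the within-group analysis shows the effect of biofeedback.

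The cost is wording only, since both arms already have gait assessments at all five visits. The drawback is that a retention claim must now hold against control, with a 95% half-width of about 0.27 SD in place of 0.195 SD under the assumptions above.

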#### Secondary outcomes

To supplement the MTC data, gait kinematics (secondary outcome variables) will be used to assess gait training effects on gait speed, stance/swing times, and joint angles at key events, foot-contact, toe-off, and MTC of the affected and unaffected limb. Baseline and retention clinical data will show how falls risk measures were influenced by feedback training. The association between the clinical tests and the biomechanical variables will be shown by correlating tripping probability and clinical measures. Medio-lateral and anterior-posterior foot pressure (COPE) shifts will reveal biofeedback effects on gait stability. A further secondary outcome is the number of falls following training. These data will be collected via monthly falls calendars for 12 months from enrolment in the study as illustrated in the SPIRIT study timeline (Fig. 2).

**Fig. 2 Fig2:**
[figure not shown]
SPIRIT study timeline. T1 to T10 gait training sessions of (up to) 10 min treadmill walking. Feedback (FB) group given visual feedback display of minimum toe clearance (MTC), No-Feedback group given no gait-related information. Gait stability assessment from plantar pressures. Clinical Tests, Borg Scales, and Falls Calendars: see text. Gait Bio. Baseline gait biomechanics variables for overground and treadmill walking, Fade MTC information reduced progressively for FB group, COPE Centre of Pressure Excursion

### Sample size calculations

In determining sample sizes, for the between-group comparisons, to detect differences in MTC a medium effect size (ES = f = 0.25) between the group effects (No-Feedback versus Feedback) across the two time points (baseline and after training) a total of 126 or 63 per group is required (G*Power [25] calculation, 2 × 2 repeated measures design, α = 0.05, power = 0.85, correlation = 0.7). To allow a 20% drop-out, we shall initially recruit 75 participants per group (*N* = 150). This sample size will also allow detection of an increase of 1 SD in MTC of the biofeedback group, compared to their pre-training. The probability of tripping [7] calculated using the pilot (stroke) participants’ data suggests that a 1 SD (0.77 cm) increase in MTC will result in significant reduction in the risk of tripping on small (1–2 cm) obstacles. A 0.77-cm increase in MTC represents approximately a 50% gain in minimum ground clearance (mean MTC = 1.4 cm) that is shown by our modelling to represent a substantial decrease in tripping risk, i.e. the probability of contacting an obstruction of a given height.

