## Methods/Design

This single-blinded parallel group RCT with 1:1 randomization will assess the effects of biofeedback on MTC following gait training. It will conform to CONSORT guidelines and has been registered on the Australian and New Zealand Clinical Trials Registry (ANZCTR): ACTRN12617000250336. Ethics approval for the study was obtained from Austin Health, Melbourne Health, and Victoria University Human Research Ethics Committees. Informed consent procedures include the provision that participants clearly understand that they are free to withdraw at any time without providing a reason. The study design flowchart is shown in Fig. 1.

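### The 126-participant calculation powers a group effect averaged over baseline and post-training, so its 85% for a medium effect does not describe the post-training comparison used to judge effectiveness

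*Protocol article*

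**What the plan says.** Under *Sample size calculations*, the protocol article sets out to detect "a medium effect size (ES = f = 0.25") for the difference "between the group effects (No-Feedback versus Feedback) across the two time points (baseline and after training"). The inputs are "2 × 2 repeated measures design, α = 0.05, power = 0.85, correlation = 0.7", and the result is that "a total of 126 or 63 per group is required". Recruitment is then raised to 150: "To allow a 20% drop-out, we shall initially recruit 75 participants per group".

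The same section adds, as a further property of this sample, that it can detect a 1 SD rise in the biofeedback group relative to its own pre-training value. It gives the pilot SD as 0.77 cm.

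Under *Data management and statistical analysis*, treadmill MTC is to be analysed by group comparisons, repeated-measures ANOVA and change scores, with walking speed as a covariate. Time has five levels, of which baseline is one. The sentence on efficacy reads "Between-group comparisons of MTC post-training will reveal effectiveness of the biofeedback gait training method in improving MTC". The primary objective, in *Background*, is whether biofeedback during gait training increases MTC.

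**The concern.** The calculation and the efficacy analysis concern different contrasts. The sample-size wording describes a group effect taken across both time points, one of which precedes training. The analysis section judges effectiveness on the post-training difference between groups. In a "single-blinded parallel group RCT with 1:1 randomization" the groups are expected to be equal at baseline, so a contrast that averages baseline in carries only half of whatever the training achieves.

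Two things are at stake. First, the stated justification for the sample attaches 85% power for a medium effect to a hypothesis that the trial does not ask about. Second, the analysis section lists several analyses of treadmill MTC without tying any of them to the calculation, so a reader who works from the sample-size paragraph could take the ANOVA group term for the treatment test. That term is diluted by the baseline.

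**Working it through.** **Inputs.** From *Sample size calculations*: f = 0.25, α = 0.05, target power 0.85, correlation ρ = 0.7, two groups, m = 2 measurements, pilot SD 0.77 cm. From *Methods/Design*: 1:1 allocation.

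**Step 1: reproduce 126.** For the repeated-measures between-factors test,

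λ = f²·N·m / (1 + (m − 1)ρ), with F on 1 and N − 2 degrees of freedom.

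- N = 126: λ = 0.0625 × 126 × 2 / 1.7 = 9.26; power 0.8555.
- N = 124: power 0.8498, just short of 0.85.

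So 126 is the smallest even total, and the plan's figure reproduces exactly.

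**Step 2: try the alternatives with the same inputs.**

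| Test | N for 85% |
|---|---|
| Between factors, m = 2 | 126 |
| Group-by-time, m = 2, λ = f²·N·m/(1 − ρ) | 24 |
| Single time point, λ = f²·N | 146 |
| Between factors, m = 5 | 112 |
| Group-by-time, m = 5 | 16 |

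Only the first gives 126, and the section's own wording agrees with it.

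**Step 3: translate f into a post-training difference.** With two groups, f = 0.25 is a difference of 2 × 0.25 = 0.5 SD in the quantity tested, here the mean of baseline and post-training. If the expected baseline difference is 0 and the post-training difference is d, the averaged difference is (0 + d)/2 = d/2. Setting d/2 = 0.5 gives d = 1.0 SD, or 0.77 cm. At N = 126 the post-training difference detectable with 85% power by this test is 0.99 SD (0.76 cm).

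**Step 4: power for a medium post-training difference.** Take d = 0.5 SD (0.5 × 0.77 = 0.385 cm), N = 126 (63 per group), two-sided 5%. The noncentrality is the standardised effect × √(63/2), and √(63/2) = 5.61.

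| Contrast | Standardised effect | Power | N for 85% | Detectable at 85% |
|---|---|---|---|---|
| Mean of baseline and post | 0.25/√0.85 | 33% | 492 | 0.99 SD |
| Post-training only | 0.5 | 79.5% | 146 | 0.54 SD |
| Change score (group-by-time) | 0.5/√(2(1 − 0.7)) = 0.5/√0.6 | 94.9% | 90 | 0.42 SD |
| Adjusted for baseline MTC | 0.5/√(1 − 0.7²) = 0.5/√0.51 | 97.4% | 76 | 0.38 SD |

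None of these is 85%. If 20% drop out of 150, 120 remain, and the change score still has 93.9% power.

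**Step 5: sensitivity to ρ.** From ρ = 0.5 to 0.9 at N = 126, the change score runs from 79.5% to above 99.9%, the baseline-adjusted analysis from 89.5% to above 99.9%, and the averaged contrast from 36% to 30%.

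**Assumptions.** Equal SDs at both times, zero expected baseline difference, no adjustment for walking speed.

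**The case against.** The best defence is that the trial loses nothing. Change scores are already among the planned analyses, and at the document's own correlation they have more than 85% power for a 0.5 SD difference, even after the full 20% loss. That stands: the defect lies in the stated justification and not in the number recruited. It is not an arithmetic slip either, since 126 is correct for the test that was entered.

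A reader might infer from the 33% that the trial would usually miss a medium effect. The document does not support this. That figure belongs to a two-time group term, which the analysis section does not name as the efficacy test. The planned ANOVA has five time points. If a 0.5 SD difference held at all four post-training visits, with ρ = 0.7 between every pair, its group term would carry 0.8 × 0.5 = 0.4 SD against an SD of √((1 + 4 × 0.7)/5) = √0.76, which gives about 72% power at 126. That is still short of 85%, and it supposes full retention.

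Nor does the 79.5% show that the named post-training comparison falls short. It is for a bare comparison and leaves out the planned walking-speed covariate, whose effect on power cannot be computed from the document.

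It can also be said that the intervention aims at a 1 SD gain, which even the averaged contrast would detect with about 85% power if controls did not change and the same SD were meant. But the sample-size section labels the between-group effect as medium. It presents "a 1 SD (0.77 cm) increase in MTC" separately, as a gain over the biofeedback group's own pre-training value. The match is conditional and is not the stated basis for 126.

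**Conclusion.** The point holds as a mismatch between the contrast that was powered and the contrast that will be analysed. The 85% belongs to the group main effect averaged over baseline and post-training, where f = 0.25 means a post-training difference of about 1 SD. It is not the power for a medium post-training difference.

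The stronger conclusion, that the sample is too small, does not follow. Under the assumptions listed with the calculation, 126 evaluable participants give about 95% power for 0.5 SD by change score and about 97% with baseline adjustment. The conclusion about the change score depends on the correlation: at ρ = 0.5 it would have about 80%, against about 90% with baseline adjustment. This should be corrected, but it does not threaten the trial.

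**What to change.** Rewrite the sample-size paragraph for the between-group difference in post-training treadmill MTC, with its own effect size and power, and name that contrast as the efficacy test. The change score would do. Adjustment for baseline MTC is preferable, because it has more power and depends less on the assumed correlation. Wording along these lines would serve:

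*The efficacy test is the between-group difference in treadmill MTC after training, adjusted for baseline MTC. With 126 evaluable participants, two-sided α = 0.05, equal SDs and a baseline to post-training correlation of 0.7, power is about 97% for a difference of 0.5 SD (about 90% if the correlation is 0.5), or 85% for 0.38 SD. The group main effect averaged over baseline is not a test of efficacy.*

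If the change score is kept, the corresponding figures are about 95% for 0.5 SD, or 85% for 0.42 SD. The cost is one reworded paragraph and one sentence in the analysis section, settled before the data are analysed. No extra participants are needed.

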**Methods:**

Participants will be aged > 18 years, have sustained a single stroke (ischemic or hemorrhagic) at least six months previously, able to walk 50 m independently, and capable of informed consent. Using a secure web-based application (REDCap), 150 participants will be randomly assigned to either no-feedback (Control) or feedback (Experimental) groups; all will receive 10 sessions of treadmill training for up to 10 min at a self-selected speed over 5–6 weeks. The intervention group will receive real-time, visual biofeedback of MTC during training and will be asked to modify their gait pattern to match a required “target” criterion. Biofeedback is continuous for the first six sessions then progressively reduced (faded) across the remaining four sessions. Control participants will walk on the treadmill without biofeedback. Gait assessments are conducted at baseline, immediately following the final training session and then during follow-up, at one, three, and six months. The primary outcome measure is MTC. Monthly falls calendars will also be collected for 12 months from enrolment.

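### Recruiting 150 does not cover a 20% drop-out from the 126 the plan requires: it leaves 120 and about 84% power, not 85%

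*Protocol article*

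**What the plan says.** The section on sample size calculations in the protocol article bases the trial on a medium effect, Cohen's f = 0.25, between the two groups, measured "across the two time points (baseline and after training"). The remaining inputs are given as "2 × 2 repeated measures design, α = 0.05, power = 0.85, correlation = 0.7". From these it concludes that "a total of 126 or 63 per group is required".

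The next sentence turns that requirement into a recruitment target: "To allow a 20% drop-out, we shall initially recruit 75 participants per group", giving N = 150. The Methods part of the abstract repeats the total: "150 participants will be randomly assigned to either no-feedback (Control) or feedback (Experimental) groups". Allocation is 1:1 (Methods/Design). The article gives no other drop-out rate, no rule for replacing participants who leave, and no other evaluable target.

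**The concern.** An allowance for drop-out should leave the required number after the loss has occurred. Here the requirement is 126, the loss is 20% and the recruitment figure is 150, and the three do not agree. The target appears to have been reached by adding about 20% to 126, when the calculation needed is to divide 126 by the proportion expected to remain.

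What is at stake is the accuracy of the sample size statement. A team that lost between 16% and 20% of its participants would believe itself within its planned allowance while already below its own requirement. Participants are asked to attend ten training sessions and assessments up to six months afterwards, so the drop-out figure is likely to be consulted when the results are read.

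**Working it through.** **Inputs**, all from the sample size section unless noted: f = 0.25; two groups; m = 2 measurements; correlation ρ = 0.7; α = 0.05; target power 0.85; requirement 126 (63 per group); drop-out 20%; recruitment 150 (75 per group; the total is also in the abstract). Allocation is 1:1 (Methods/Design).

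**Step 1. Reproduce the 126.** The article names G*Power but not the option chosen. For the between-groups test in a repeated-measures ANOVA, the noncentrality parameter is

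λ = f² × N × m / (1 + (m − 1)ρ), with 1 and N − 2 degrees of freedom.

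| Evaluable N | λ | Power |
|---|---|---|
| 124 | 0.0625 × 124 × 2 / 1.7 = 9.12 | 0.8498 |
| 126 | 0.0625 × 126 × 2 / 1.7 = 9.26 | 0.8555 |

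The smallest total with equal groups that reaches 0.85 is therefore 126, exactly as stated. The within-subject and interaction options both give N = 24, so the between-groups option is evidently the one used.

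**Step 2. Apply the stated drop-out to the stated recruitment.**

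- In total: 150 × (1 − 0.20) = 120, which is 126 − 120 = 6 short.
- Per group: 75 × 0.80 = 60, which is 63 − 60 = 3 short.

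**Step 3. Recruitment needed for the requirement to survive a 20% loss.**

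- In total: 126 / 0.80 = 157.5, so 158.
- Per group: 63 / 0.80 = 78.75, so 79.

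**Step 4. Loss that 150 can absorb.** 1 − 126/150 = 0.16, that is 24 participants. A 20% loss is 30.

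**Step 5. Power at the number actually left.** At N = 120, λ = 0.0625 × 120 × 2 / 1.7 = 8.82 and power is 0.838. That is 1.2 percentage points below the stated 0.85 and 1.7 points below the 0.855 at 126.

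**Cross-check.** The between-groups test compares each participant's mean of the two measurements. With f = 0.25 for two groups, the standardised difference is 0.5, and the SD of that mean is √((1 + 0.7)/2) = √0.85. The normal approximation for two means gives power 0.861 at 63 per group and 0.844 at 60 per group. The drop has the same size, and 60 per group again falls short of 0.85.

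**Likely origin.** 126 × 1.20 = 151.2 (75.6 per group), close to 150. This is an inference; the article does not show how 150 was obtained. Even 151.2 would leave only 151.2 × 0.80 = 121 after a 20% loss.

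**The case against.** The case against does not dispute the arithmetic. It argues that the point carries little weight, on four grounds.

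- **The loss of power is very small.** A fall of 1.2 points is minor beside the uncertainty in a conventional medium effect and a correlation of 0.7 for which no derivation is shown. Power of 0.80 needs only 110 evaluable, so 150 could lose 40 participants (27%) before falling below that level. This stands, and it limits the importance of the point.
- **The 126 belongs to a test that averages baseline and post-training.** The analysis section judges effectiveness by the groups' post-training MTC. If that comparison were adjusted for baseline MTC, 120 evaluable would give power of about 0.967 for a 0.5 SD difference at ρ = 0.7, against 0.974 at 126. This too shows that six participants matter little. The article does not state baseline MTC as a covariate, however, and the choice of test for the power calculation is a separate question. The sentence still contradicts the requirement that the plan set for itself.
- **The 20% may mean recruiting about 20% extra.** 150/126 is 1.19, so 150 fits that reading approximately. But the text speaks of drop-out, and if a fifth of participants do drop out, 120 remain.
- **The 20% may refer to the whole six-month follow-up.** Losses by the post-training assessment, after 5–6 weeks of training, could then be smaller, and 126 might still be reached. This is possible, but the article does not say so, and the drop-out sentence directly follows a calculation based on baseline and post-training only.

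These points bear on how much the error matters. None of them makes the stated figures agree.

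**Conclusion.** The point holds. At N = 150, a 20% drop-out and 85% power cannot both be achieved on the plan's own figures: 120 remain where 126 are required, the tolerable loss is 16%, and power at 120 is 83.8%.

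The shortfall in numbers rests only on figures the article states, reading drop-out in the usual way as a share of those recruited. The power figure also assumes the between-groups option in G*Power, which the article does not name but which reproduces 126 exactly. This is a small error in a stated figure, does not leave the trial seriously underpowered, and gives no reason to change the design.

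**What to change.** Keep recruitment at 150 and correct the drop-out sentence in one of two ways:

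- state that recruiting 150 (75 per group) allows for a 16% drop-out while retaining 126 evaluable; or
- keep the 20% and state that it leaves 120 evaluable (60 per group), with power of about 84% (0.838) on the same inputs.

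It would help to add which assessment the drop-out rate refers to. The cost is one sentence and no additional participants. If the sponsor prefers to keep both the 20% and the 85%, the target becomes 158 (79 per group), 8 more than planned; the small gain in power does not make that necessary.
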